**Randomization **

Eligible patients who fulfill the inclusion criteria will be enrolled in the study. At first, the included patients will be randomized (1:1) into intervention or control groups. We will use a permutated block randomization approach to stratify subjects according to migraine severity with a block size of 4. We will use a table of random numbers to perform random assignment. In addition, patients will be enrolled and assigned into intervention and control groups by a well-trained nutritionist. Allocation concealment will be performed by sequentially numbered containers. 

**Intervention**

Patients in the intervention group will receive one capsule/day containing 250 mg phytosomal curcumin (250 mg containing 20% curcuminoids and 20% phosphatidylserine; Indena SpA, Milan, Italy), for 8 weeks. On the other hand, patients in the control group will receive one capsule/day containing 250 mg maltodextrin, for the same duration. Participants will be asked to take each capsule one hour after breakfast. Moreover, we will instruct the patients in both groups to follow their usual diet and physical activity as well as their medication therapy exactly as their neurologist prescribed. 

**Figure 1 F1:**
[figure not shown]
Study Flow Diagram

**Blinding**

Capsules (curcumin and placebo) will be labeled A and B by the company in the same format of the packages; in addition, capsules will be manufactured in the same shape, size, color and odor. Investigators, patients, laboratory staff, outcome assessors, and data analyzers will be blinded to treatment assignment until final analyses will be conducted. 

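### A constant A/B product code is not reconciled with the numbered containers: linking one letter to curcumin could unmask up to 60 of 60 patients, and upcoming letters are partly predictable if the letter is readable at dispensing

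*Protocol article*

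**What the plan says.** All of this is in the protocol article.

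- **Blinding, product code:** "Capsules (curcumin and placebo) will be labeled A and B by the company in the same format of the packages".
- **Blinding, appearance:** "capsules will be manufactured in the same shape, size, color and odor".
- **Blinding, who is masked:** "Investigators, patients, laboratory staff, outcome assessors, and data analyzers will be blinded to treatment assignment until final analyses will be conducted". The nutritionist who assigns patients is not named separately.
- **Randomization, ratio and blocks:** "the included patients will be randomized (1:1) into intervention or control groups", and "We will use a permutated block randomization approach to stratify subjects according to migraine severity with a block size of 4". The number of severity strata is not given.
- **Randomization, who assigns:** "patients will be enrolled and assigned into intervention and control groups by a well-trained nutritionist".
- **Randomization, concealment:** "Allocation concealment will be performed by sequentially numbered containers".

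The article does not say whether the letter can be seen on a numbered container, or whether each stratum has its own series of containers.

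**The concern.** Numbering conceals the sequence only if nothing else on the container shows the group. A readable A or B would show it, and a known block of 4 would then let the person who enrols work out some of the next letters. Selective enrolment does not require knowing what a letter means. Any belief about B, right or wrong, is enough to influence who is entered when B comes next.

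The second problem does not depend on prediction. With one letter per product for the whole trial, a single link between letter and product identifies both arms. Unique container numbers do not have this weakness.

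Many outcomes are exposed. Attack frequency and duration during the intervention, the pain VAS, HIT-6, MSQ, DASS-21 and PSQI are all reported by the patient, so they are sensitive to selection at entry and to loss of masking.

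**Working it through.** The plan states no figure for predictability or unmasking, so there is nothing of its own to reproduce first.

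**Inputs.** Block size 4 and ratio 1:1 come from Randomization, and the total of 60 from the Abstract and the opening of Materials and Methods. Assumed for steps 1 to 3: the letter is readable, and the enroller knows the block size and keeps track within each stratum.

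**Step 1: letters fixed in advance.** A 1:1 block of 4 has six equally likely orders: AABB, ABAB, ABBA, BAAB, BABA, BBAA.
- Positions 1 and 2 are never fixed.
- Position 3 is fixed when the first two letters match (AABB, BBAA): 2/6 = 1/3.
- Position 4 is always fixed: 1.
- Share = (0 + 0 + 1/3 + 1)/4 = 1.333/4 = 33.3%. Over 60 patients, 60 × 1/3 = 20.

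**Step 2: letters guessed correctly.** The guess is always the letter with more places left in the block.
- Position 1: 1/2.
- Position 2: guess the opposite of the first letter, correct in 4 of 6 orders = 2/3.
- Position 3: 1/3 × 1 + 2/3 × 1/2 = 2/3.
- Position 4: 1.
- Mean = (1/2 + 2/3 + 2/3 + 1)/4 = 70.8%, or 42.5 of 60. Chance gives 50%, or 30 of 60.

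**Step 3: incomplete blocks.** Steps 1 and 2 treat the 60 patients as 15 full blocks. Stratification leaves some blocks unfinished. Simulation (4,000 trials per setting, strata equally likely, number of strata assumed) gives:

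| Strata | Fixed in advance, block 4 | Guessed, block 4 | Guessed, blocks of 4 or 6 at random |
|---|---|---|---|
| 1 | 20.0 of 60 | 42.5 (70.8%) | 41.4 (69.1%) |
| 2 | 19.2 of 60 | 42.1 (70.2%) | 41.2 (68.6%) |
| 3 | 18.8 of 60 | 41.9 (69.9%) | 40.9 (68.2%) |

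The last column guesses from the running imbalance within the stratum. While the letter stays visible, varying the block size barely lowers the guessing rate.

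**Step 4: letter hidden.** If the numbered containers conceal the letter before and after dispensing, the enroller has no history to count. No letter is fixed in advance, and guessing falls to 50% (30 of 60).

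**Step 5: one link between letter and product.**
- Constant A/B code: knowing that one letter is curcumin makes the other placebo, so every patient whose letter is known is identified. The upper bound is 30 + 30 = 60 of 60.
- Unique numbers: one link identifies 1 of 60 with certainty. If the block of 4 is known, the other three patients in it share that patient's arm with probability (2 − 1)/3 = 1/3 instead of 1/2. That shifts the odds but identifies no one.

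**The case against.** The two sections can both be true. The company may supply two coded products that are then packed into numbered containers showing no letter. A condensed article need not describe the packing or say who holds the list, and those gaps are not the complaint.

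A reader might infer that the packs carry nothing but A or B and that upcoming allocations can therefore be predicted. The article does not support that. It promises numbered containers and nowhere says that the letter is legible on them. Steps 1 to 3 also describe the next letter, not the next treatment: with matched capsules, the letter's meaning stays masked until something links it to a product.

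A reader might also infer that one code break necessarily unmasks the whole trial. That too is stronger than the text allows. It reaches only people who know patients' letters as well, and the Ethics approval section says that data, specimens and reports carry a unique patient ID. Nothing shows that laboratory staff or assessors see letters.

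Two further points stand. Nitric oxide, on which the trial was sized, is measured by ELISA and is less exposed than the questionnaires. Analysts are already to be masked until the final analyses, so nothing needs adding there.

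These points make the predictability figures conditional and the 60 an upper bound. They do not remove the unreconciled sections or the weakness of a constant two-letter code.

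**Conclusion.** The concern holds in conditional form. The article fixes a constant two-letter product code, one published block size of 4, and one role that both enrols and assigns. It does not reconcile the letters with the numbered containers.

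- **If the letter is readable at dispensing,** and the enroller knows the block size and tracks the strata, about 19 to 20 of 60 upcoming letters are determined and about 71% can be guessed (about 70% with two or three strata), against 50%. If the letter is hidden, these figures do not apply.
- **Regardless of predictability,** linking one letter to curcumin unmasks every patient whose letter is known, up to 60 of 60, against 1 of 60 with unique numbers. This is the firmer part. It assumes only that each letter denotes one product throughout.

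The labelling is the main problem and the fixed block size is secondary. The labelling should be changed: a better method is available at little cost, and most of the clinical outcomes are self-reported.

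**What to change.** Align the Randomization and Blinding sections on one scheme.

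1. The company labels each container only with a unique number taken from the severity-stratified list. No A/B letter is visible to clinic staff, patients or assessors.
2. The key from number to arm is held outside the clinics until database lock.
3. As a secondary measure, use randomly varying block sizes (for example 4 and 6) within stratum, not disclosed to the nutritionist who enrols. On its own this is not enough: with visible letters about 68 to 69% would still be guessed correctly, and a link between letter and product would still reach every patient whose letter is known.

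If the containers already hide the letter, one sentence saying so settles the predictability question. Replacing the constant code is still worthwhile wherever patients' letters are recorded or known.

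The cost is a new label list from the company that already labels the product, a new random list, and slightly larger possible imbalance between arms at the end of the trial from the varying blocks. No extra staff are needed.

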**Ethics approval**

The whole protocol has been approved and accepted by the ethics committee of Isfahan University of Medical Sciences (IR.MUI.RESEARCH.REC.1400.110). The study is registered in the Iranian Registry of Clinical Trials, IRCT (IRCT20201129049534N2). All patients will be asked to fill the written consent before being included in the study. We will store data of the participants at the security site. We also will use a unique ID number for each patient for the collected data, laboratory specimens, and reports. Just the research teams will have access to the collected data during the course of the research and these will be remained strictly confidential. The corresponding author will also have access rights to the dataset. In addition, to enable international prospective meta-analyses, the corresponding authors will share the anonymous data with other researchers. 

**Safety consideration**

Curcumin is safe even at high concentrations as it has been previously shown that administration of 8,000 mg curcumin/day for 3 months was safe without any toxicity. Just some gastrointestinal discomfort, specifically nausea and diarrhea was occurred (Hsu and Cheng, 2007 ▶; Chainani-Wu, 2003 ▶). Thus, no considerable adverse effects will be anticipated for the consumption of curcumin and placebo capsules at the mentioned doses. However, if minor side effects occur, it will be reported to the Ethics Committee of Isfahan University of Medical Sciences for decision-making.

**Power calculation and sample size estimates**

Sample size was calculated using the formula suggested for randomized clinical trials considering the type I error of 5% (α = 0.05) and Type II error of 20% (β = 0.2; power = 80%). Nitric oxide (NO) level was also considered a main outcome, and based on a previous study (Zareie et al., 2020 ▶), sample size was calculated 23 persons for each group. With potential dropout, finally 30 patients will be assigned in each group.

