**Materials and Methods::**

This is a randomized, double-blind, placebo-controlled, clinical trial in which, 60 patients with migraine will be assigned to receive a daily dose of 250 mg of phytosomal curcumin for 8 weeks (intervention group) or 250 mg maltodextrin as a placebo for the same duration (control group). Before and after the study, frequency, duration, and severity of the attacks, quality of life and sleep, mood status, high-sensitivity C-reactive protein (hs-CRP), Nitric Oxide (NO), and oxidative stress factors will be measured.

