**Statistical methods**

The analysis will eventually be performed in the form of Intention-To-Treat (ITT) and Per-Protocol (PP) using the SPSS software, version 22 (SPSS Inc, Chicago, IL, USA). Quantitative data will be reported as mean±standard deviation (SD), and qualitative data will be presented as frequency and percent. Normality of the data will be assessed using Kolmogorov-Smirnov test. Paired t-test will be applied to evaluate the differences in each group before and after intervention. Independent T will be used to show the baseline and endpoint differences between the two groups. We will apply analysis of covariance (ANCOVA) to show differences between two treatment groups after adjusting for confounding variables. P-value less than 0.05 will be considered statistically significant. 

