**Figure 2 F2:**
[figure not shown]
Schematic summary of pathways depicting the possible effects of phytosomal curcumin on migraine and its potential related mechanisms. As shown in the figure, curcumin, as a natural, accessible, safe, and inexpensive phytochemical has some limitations including low bioavailability, instability at physiological pH, and low solubility in water; thus, its combination with phosphatidylserine can effectively reduce the limitations of using curcumin. Phytosomal curcumin might have beneficial effects on migraine attacks and complications through several mechanisms, including reduction in oxidative stress, neuroinflammation, and neurotoxicity. On the other hand, it increases autophagy and brain-derived neurotrophic factor (BDNF), nerve growth factor (NGF), and glial cell line-derived neurotrophic factor (GDNF), which all causes growth, maturation (differentiation), and maintenance of nerve cells (neurons) and promote survival of these cells

Although this study will be the first randomized double-blind clinical trial investigating the effect of phytosomal curcumin on migraine, some limitations such as relatively short duration of the intervention and lack of long-term follow-up should be acknowledged. In addition, considering the ethical issues, the effect of phytosomal curcumin as a monotherapy approach will not be feasible to be assessed.

The protocol for a double-blinded placebo-controlled trial design is described here, in which the effects of phytosomal curcumin supplementation will be assessed on clinical symptoms as well as inflammatory and oxidative stress biomarkers of patients with migraine. It is expected that oral supplementation with 250 mg/day of phytosomal curcumin for 8 weeks will result in relieving migraine signs and symptoms as well as reduction of inflammation and oxidative stress. Findings of the current study will provide evidence-based information in terms of the efficacy of curcumin as a complementary treatment in patients suffering from migraine.

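### Nitric oxide is the only outcome sized but is not fixed as the sole primary, and one unranked P<0.05 rule covers 15 outcomes

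*Protocol article*

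**What the plan says.** Only the section Power calculation and sample size estimates gives any outcome a rank: "Nitric oxide (NO) level was also considered a main outcome". With type I error 5% and power 80%, and relying on an earlier study, "sample size was calculated 23 persons for each group". Then: "With potential dropout, finally 30 patients will be assigned in each group". No difference or standard deviation for NO is given, and the test is not described as one- or two-sided.

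The Abstract names the attack characteristics, quality of life, sleep, mood and laboratory markers in one list, with none marked as primary. The outcome sections define the individual measures.

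The Statistical methods section plans both ITT and PP analyses. It compares groups by independent t-test at endpoint and also by ANCOVA with adjustment for confounders. Its one decision rule is "P-value less than 0.05 will be considered statistically significant". Neither the tests nor the analysis sets are put in order.

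The title and objective lead with clinical symptoms or signs. The last paragraph of the Discussion expects that the supplement "will result in relieving migraine signs and symptoms as well as reduction of inflammation and oxidative stress".

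**The concern.** The word *also*, together with the indefinite *a main outcome*, suggests that at least one other main outcome exists, yet none is named. A reader cannot tell whether NO is the primary outcome, one of several, or simply the variable that was convenient for the calculation.

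This matters for two reasons. First, the primary outcome defines the one test to which the 5% error rate and the 80% power belong. If it is left open, the choice can be made after the results are known, and no later analysis fully repairs that. Second, the article expects clinical relief, but its only power statement concerns a blood marker. The 80% could be read as covering the clinical outcomes, and nothing in the article supports that.

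**Working it through.** **1. The plan's own figure.** The 23 per group can be neither confirmed nor refuted, because the NO difference and SD are missing. It can be solved backwards. With n = 2(z_α + z_β)²/d², d = √[2(z_α + z_β)²/n]:

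- Two-sided 5%: d = √[2 × (1.960 + 0.842)²/23] = 0.83; the t-test version gives 0.84.
- One-sided 5%: d = √[2 × (1.645 + 0.842)²/23] = 0.73; the t-test version gives 0.74.

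The stated power therefore holds for a standardised NO difference of about 0.84 if two-sided, or about 0.74 if one-sided. Going from 23 to 30 per group implies an allowance of 1 − 23/30 = 23% dropout.

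**2. Number of outcomes**, from the assessment sections:

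| Section | Outcomes | Count |
|---|---|---|
| Migraine assessment | attack frequency, attack duration, VAS, HIT-6 | 4 |
| Quality of life | MSQ total | 1 |
| Mood status | DASS-21 stress, anxiety, depression | 3 |
| Sleep quality | PSQI | 1 |
| Laboratory assessment | hs-CRP, TAC, TOS, MDA, SOD, NO | 6 |
| Total | | 15 |

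**3. Chance of at least one nominal positive**, with no true effect on any outcome and one two-sided test per outcome at 0.05.

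Independent outcomes: 1 − 0.95^15 = 0.537. Counting DASS-21 as a single score leaves 13 outcomes: 1 − 0.95^13 = 0.487.

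The outcomes will be correlated, and the article gives no correlations. Taking the 15 test statistics as normal with an assumed common correlation r:

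| Assumed r | Chance of at least one P<0.05 |
|---|---|
| 0 | 54% |
| 0.1 | 52% |
| 0.3 | 46% |
| 0.5 | 36% |
| 0.7 | 26% |
| One named primary | 5% |

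These figures count each outcome once. Allowing a second test (t-test or ANCOVA) or a second analysis set (ITT or PP) to supply the positive result can only raise them.

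**4. What the 80% does not cover.** The article gives no expected clinical effect. For illustration, at an assumed standardised difference of 0.5, a two-sided t-test has about 38% power with 23 per group and 48% with 30.

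**The case against.** The strongest reply is that NO is already the primary outcome in practice. It is the only outcome called main and the only one sized, and *also* may merely add NO to the inputs listed in the sentence before it. This has force. It is the reason the remedy starts from NO, and the gap may be one of wording. But the sentence stops short of making NO the sole primary, and no other section settles it.

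A second reply is that multiplicity control for secondary outcomes, the choice between t-test and ANCOVA, and the lead analysis set are commonly left to an analysis plan, which is not shown here. This stands: their absence from the article is not counted as a fault. Designating the primary outcome is different, because the sample size depends on it.

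Some stronger readings are tempting but not supported:

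- A reader might infer that the plan declares success if any one outcome is significant. It does not say so; the 0.05 sentence is a general reporting threshold.
- A reader might infer that a false positive is about as likely as not. That holds only if the outcomes are nearly independent, and several are likely to move together, such as the headache measures, the three DASS-21 subscales and the oxidative-stress markers.
- A reader might multiply outcomes, tests and analysis sets into a large count of P values. Those results come from the same patients and are strongly related, so the count is not an error rate.
- A reader might conclude that a clinical outcome should replace NO as primary. The article gives no basis for sizing one, and the present sample was not chosen for it.

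**Conclusion.** The concern holds in a limited form. The article gives NO the status of a main outcome and sizes the trial on it, but does not fix it as the single primary, and it sets one unranked threshold across 15 outcomes.

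The chance of at least one nominal positive is 54% under independence and about 26% to 52% for common correlations of 0.7 down to 0.1. Even the lowest of these is about five times the nominal 5%. The range rests on no true effect on any outcome, one two-sided test per outcome, and correlations that are assumed.

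The 80% power is a statement about NO alone. It cannot be carried over to the symptoms that the Discussion expects to improve.

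**What to change.** Before unblinding:

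1. State that NO is the single primary outcome, tested once by ANCOVA in the ITT set at two-sided 0.05.
2. Label all other outcomes, the endpoint t-tests and the PP analyses as secondary or supportive, so that no efficacy claim rests on an unadjusted P<0.05 among them.
3. State that the 80% power applies to NO only, say whether the calculation was one- or two-sided, and give the NO difference and SD behind the 23 per group.

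The change is to wording; sample size and data collection stay as they are. The real cost is in interpretation: clinical results become supportive rather than confirmatory, and the closing expectation in the Discussion should be worded to match.

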**Assessment of quality of life**

The Migraine-Specific Quality of Life (MSQ) questionnaire will be used to assess the quality of life of migraine patients. The questionnaire consists of 14 questions that assess the quality of life of patients in the last month. The validity of this questionnaire in Iran has been examined by Zandifar et al. (Zandifar et al., 2013 ▶). For each question, a score of one (never) to six (always) is considered, then the sum of the scores of the questions, which is from 14 (minimum total) to 84 (maximum total), will be considered. The sum of the initial scores will be converted to a scale of zero to one hundred, and finally a higher score will indicate a higher quality of life (Zandifar et al., 2013 ▶). To convert the initial score from zero on one hundred scale, we will follow this method: Individual score minus 14 (lowest total score) divided by 70 (distance between the lowest (14) and the highest total score (84)) multiplied by 100. 

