**Assessment of mood status (stress, anxiety, and depression)**

A modified DASS-21 questionnaire for Iran will be used to assess mood at the beginning and end of this study (Samani and Joukar, 2007). The DASS-21 subscales consist of 21 questions, seven questions for stress, seven for anxiety, and seven for depression. Each question is scored from zero (does not apply to me at all) to 3 (absolutely applies to me). The subscales should be doubled, then the severity of the symptoms can be determined as shown in Table 2 (Lovibond and Lovibond, 1995 ▶).

**Table 1 T1:** Timeline and applied tests

**Activity**	Time (Week)								
	0	1	2	3	4	5	6	7	8
**Enrollment**	*								
Eligibility screening Informed consent Randomization Allocation	*								
	*								
	*								
	*								
Sociodemographic	*								
Intervention		*	*	*	*	*	*	*	*
Placebo (maltodextrin, 250 mg)		*	*	*	*	*	*	*	*
Intervention (250 mg phytosomal curcumin)		*	*	*	*	*	*	*	*
Compliance and side effects		*	*	*	*	*	*	*	*
Laboratory tests	*								*
VAS	*								*
HIT-6	*								*
MSQ	*								*
DASS-21	*								*
Food record	*								*
Physical activity recall	*								*

**Table 2 T2:** Intensity of each subscale for assessment of mood status

**Severity **	**Depression**	**Anxiety**	**Stress**
**Normal**	0-9	0-7	0-14
**Mild**	10-13	8-9	15-18
**Medium**	14-20	10-14	19-25
**Intense**	21-27	15-19	26-33
**Very intense**	+28	+20	+34

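### Excluding patients with under 80% compliance conflicts with the promised ITT, and with most outcomes measured only at weeks 0 and 8 the ITT may reduce to completers

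*Protocol article*

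**What the plan says.** **Timing of outcomes.** Table 1 marks laboratory tests, VAS, HIT-6, MSQ and DASS-21 at weeks 0 and 8 only. The text agrees for HIT-6 (Migraine assessment), DASS-21 (Assessment of mood status) and blood sampling (Laboratory assessment). Sleep quality by PSQI is also before and after only (Assessment of sleep quality). Attack frequency and duration are the exception: patients fill in questionnaires on them during treatment. The Table 1 row "Compliance and side effects" is marked in each of weeks 1 to 8.

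**Size.** Power calculation and sample size estimates names nitric oxide as a main outcome and reports that "sample size was calculated 23 persons for each group". It then adds: "With potential dropout, finally 30 patients will be assigned in each group". No dropout rate is stated.

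**Analysis.** Statistical methods promises two analysis sets, ITT and per protocol: "The analysis will eventually be performed in the form of Intention-To-Treat (ITT) and Per-Protocol (PP"). The methods are paired t-test, independent t-test and ANCOVA.

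**Exclusions.** The last exclusion criterion is compliance with the intervention below 80%. Another is any change in drug treatment.

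**The concern.** Compliance with the capsules cannot be known at screening, so the 80% criterion can act only after patients have been randomised. Applied as written, it removes randomised patients for what happened on treatment. An ITT analysis is meant to prevent exactly that. The criterion on changed drug treatment raises the same question if it is applied after randomisation.

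The schedule makes this matter more. For the laboratory markers and all the Table 1 questionnaires there is a single measurement after baseline. A patient who is removed or lost before week 8 has none, and no later analysis plan can create data that were never collected. The planned tests would then compare those who stayed. If the reasons for leaving differ between the arms and are related to outcome, the protection of randomisation is lost under an ITT label.

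**Working it through.** **Inputs.** α = 0.05, power 80%, 23 evaluable and 30 randomised per arm (Power calculation and sample size estimates); 1:1 allocation (Randomization). Two-sided testing is assumed, since the article does not say. Normal approximation throughout.

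**1. The step from 23 to 30.** 30 − 23 = 7 per arm; 7/30 = 23.3%, or 14 of 60 overall. Check: 23/(1 − 0.233) = 30. With this formula a 20% rate gives 29 and a 25% rate gives 31. The other common formula, 23 × 1.30 = 29.9, also rounds to 30. So 30 is arithmetically coherent, but 23.3% is inferred from the numbers and not stated.

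**2. The effect implied by 23 per arm.** No difference or SD for nitric oxide is given, so 23 cannot be reproduced directly. Solving back:

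d = (1.960 + 0.842) × √(2/23) = 2.802 × 0.2949 = 0.826 SD.

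**3. What the extra patients do.** If all 7 are lost in each arm, 23 remain and power for 0.826 SD is still 80%. With no loss, power at 30 per arm is about 89%. The inflation therefore covers power. It does nothing about who is lost.

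**4. Size of a possible bias.** Let m = 7/30 be missing in each arm. In one arm let the missing differ from the completers by k SD; in the other let loss be unrelated to outcome. The completer mean in the first arm is then off by m × k. With 23 per arm the standard error is √(2/23) = 0.295 SD. With b = bias/0.295, the type I error is 1 − Φ(1.96 − b) + Φ(−1.96 − b).

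| k (SD, assumed) | Bias = 0.233 × k (SD) | Share of 0.826 SD | Two-sided type I error |
|---|---|---|---|
| 0.25 | 0.06 | 7% | 5.4% |
| 0.5 | 0.12 | 14% | 6.8% |
| 1.0 | 0.23 | 28% | 12.4% |

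If the loss acts alike in both arms, the two shifts cancel and the bias in the difference is zero.

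**5. The texts side by side.** Exclusion criteria: compliance under 80% excludes. Statistical methods: ITT and per protocol are both to be reported. An 80% threshold fits a per-protocol set. As a criterion for being in the trial at all, it would leave the two sets nearly identical.

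**The case against.** The strongest reply is that the article is a condensed protocol. The definition of the ITT set, the handling of missing values and follow-up after stopping are commonly left to the full protocol or analysis plan, and their absence is no fault. That stands. Measurement before and after is also a legitimate design for an 8-week trial, and attack frequency and duration are collected during treatment, so early stoppers may leave partial data on those outcomes.

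A reader might infer more than the text supports, in four ways:

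- *Patients who stop the capsules leave no outcome.* Nothing bars a week-8 visit after stopping, and Laboratory assessment plans both blood samples for every subject.
- *The trial expects to lose 23% per arm.* That figure is a back-calculated allowance, not a forecast.
- *The bias approaches half the detectable effect.* Removing exactly the worst 7 of 30 shifts a normal mean by φ(0.73)/(1 − 0.233) = 0.40 SD. That requires perfect selection on outcome in one arm and purely random loss in the other.
- *Gastrointestinal effects will drive dropout from curcumin.* Safety consideration mentions nausea and diarrhoea from earlier work at 8,000 mg/day and anticipates no considerable adverse effects at the trial's doses.

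What the objection does not remove is the conflict inside the article. A post-randomisation compliance exclusion and an ITT analysis cannot both be applied as written, and the two-point schedule is fixed by the text rather than left open.

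**Conclusion.** The point holds in a limited form. The compliance exclusion conflicts with the ITT, and for all outcomes except attack frequency and duration a patient not measured at week 8 contributes nothing after baseline to the planned tests. The ITT may therefore reduce to completers; the article does not say that it will.

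The bias of 0.06 to 0.23 SD, with type I error of 5.4% to 12.4%, rests on three assumptions that the article neither states nor rules out: the full allowance of 7 of 30 is lost in each arm, loss is related to outcome in one arm only, and the missing differ from completers by 0.25 to 1.0 SD. Less loss, or loss that acts alike in both arms, makes the bias smaller or zero. The matter should be corrected because it must be settled before patients leave and the correction is cheap.

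**What to change.** 1. Reconcile Exclusion criteria with Statistical methods: let compliance below 80% define only the per-protocol set, and say whether the criterion on changed drug treatment applies at screening only.
2. State that stopping the capsules is not withdrawal from the study. Invite every randomised patient who has not withdrawn consent to the week-8 blood draw and questionnaires, whatever the compliance.
3. Record the date and reason of stopping at the weekly compliance check.
4. State the dropout rate behind the step from 23 to 30.
5. Label any analysis restricted to patients with a week-8 value as completers, not ITT.

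A visit at the moment of stopping would not replace week 8 in an early stopper: the MSQ items "assess the quality of life of patients in the last month", which would partly cover time before treatment.

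Optionally, collect VAS and HIT-6 at the week-4 compliance check and analyse those two outcomes with a mixed model. This does not help nitric oxide or patients lost before week 4, and Table 1 does not show whether that check is a visit.

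**Cost.** A few sentences of protocol text and some effort to bring discontinued patients back. Keeping them also dilutes the estimated effect. In the extreme case where 7 of 30 treated patients stop and show no effect, 0.826 SD becomes 0.826 × 23/30 = 0.63 SD, and power with all 30 per arm measured is about 69%. With fewer stopping, the dilution is smaller.
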